### 14.4. Planned Analyses

Information summarizing planned analyses is described below. Further details regarding the analyses and plans for additional analyses will be contained in the PPMI Data Analysis Plan.

- 14.4.1. **Comparison of baseline characteristics among various subsets.** The first set of analyses will involve a comparison of baseline characteristics among the various subsets enrolled into the study. Continuous variables will be examined using a t-test and dichotomous variables will be examined using a chi-square test. Appropriate assumptions will be assessed for each comparison and any necessary adjustments (i.e., transformations) will be made prior to analysis. All analyses will be conducted at the 0.05 level.
- 14.4.2. **Comparison of short-term change in progression endpoints.** The second set of analyses will examine the short-term change during the first six months

for each progression endpoint. For continuous progression endpoints, the change over time will be modeled using a mixed model approach. For dichotomous progression endpoints, a logistic regression model will be fit. For each 'full' model of interest, an initial model will consist of all baseline characteristics, an indicator variable for whether the subject is a PD patient or healthy control, and all possible two-way interactions. We will utilize backwards selection to build a model for each progression endpoint.

- 14.4.3. **Examination of whether short-term change in progression endpoints is predictive of change in long-term endpoints.** The third set of analyses will examine whether short-term changes in the progression endpoints are predictive of changes in long-term endpoints in the MDS-UPDRS score. This analysis will examine a subset of the progression endpoints. Only progression endpoints that show differences between subsets will be considered (since for example, a marker that doesn't distinguish PD patients from healthy subjects would not be thought to be a biomarker for long-term outcome in PD patients). All progression endpoints that meet these criteria will be modeled using a process similar to that described above. The primary focus will be on the long-term change in the UPDRS score. However, additional long-term endpoints may be considered as well. Because this modeling process involves longer term endpoints, which would be much harder to replicate, a ten-fold cross validation procedure will be used to test the predictive validity of each model. If successful, the final model will provide a subset of one or more short-term progression endpoints that are predictive of the change in one or more of the long-term endpoints. This would suggest that these short-term progression endpoints are valid biomarkers for future studies of interventions in PD patient populations.
- 14.4.4. **Examination of PD Subsets.** Each of the first three sets of analyses will be repeated comparing subsets of PD subjects, rather than PD subjects vs. healthy subjects. If successful, the final model from these subset comparisons will determine whether some of the short-term progression endpoints are more predictive of long-term change in the MDS-UPDRS score for some subsets of PD subjects and less predictive for other subsets of PD subjects.
- 14.4.5. **Calculation of the proportion of SWEDD subjects that have a change in diagnosis over the 24-month evaluation period.** The analysis will involve identifying all SWEDD subjects that have a change in diagnosis from PD to another diagnosis. The percentage and 95% confidence interval will be reported. The other possible diagnoses will be further divided into 2 categories: 1) Other parkinsonian syndrome with a dopamine transporter deficit; 2) Other condition without a dopamine transporter deficit. The same information will be reported as well by these two categories.
- 14.4.6. **Exploratory analysis of Prodromal subjects that phenoconvert.** The analysis will involve estimating the percentage of Prodromal subjects that

phenoconvert to PD within 2 years. The percentage and 95% confidence interval will be reported.

**14.4.7. Exploratory analyses of biomarkers for predicting phenoconversion among Prodromal Subjects.** This set of analyses will examine whether short-term changes in the progression endpoints are predictive of phenoconversion among Prodromal subjects. All progression endpoints will be considered. The examination will involve fitting a logistic regression model for phenoconversion, with each progression endpoint serving as a covariate.

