The table below provides generic information about the detectable effect sizes for three types of statistical analysis that may be performed on the PPMI data. For each analysis the two-sided alpha level is set to 0.05 and the beta level to 0.80. The first column gives the total sample size assumed to be available for the analysis, in the first two rows either 400 (total PD sample) or 300 (PD sample after allowance for 25% withdrawals). The third and fourth rows of the table correspond to the total sample size of 600 (400 PD, 200 HC) when, respectively 75% and 100% of the subjects are available for analysis. The second column gives the detectable correlation coefficient between two continuous measures (e.g., change in striatal  $\beta$ -CIT uptake vs. change in total MDS-UPDRS). The third column gives the detectable difference in prevalence rates of some characteristic (e.g. presence of dopaminergic side effects) between two “halves” of the sample (e.g. the younger patients vs. the older patients, with age dichotomized at the median for the entire group). For the first two rows the third column gives the detectable “effect size”, expressed as ratio of difference in means to standard deviation, for comparing two “halves” of the sample (e.g. younger vs. older patients as above) in relation to a continuous measure (e.g. change in total MDS-UPDRS). For the third and fourth row the comparisons are between PD patients and HC. The table suggests that the PPMI trial is adequately powered to detect effects that would generally be of clinical interest. While possible that smaller effects than those listed in the table might also be of clinical interest, it was determined that the added power for these comparisons did not offset any additional costs and logistical issues that would accompany a larger study in this population. Rather, the proposed study should prove to be effective for screening a large number of variables and identifying those that show the most promise for further exploration in follow-up studies.

| Total sample size | Detectable Correlation | Detectable Difference in Prevalence | Detectable Difference in Means (Standardized) |
|--------------------------|-------------------------------|--------------------------------------------|------------------------------------------------------|

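### Section 14.4.2 starts backward selection from a model with all two-way interactions, which is too large for the available subjects: not estimable on a long baseline list, badly overfitted on a short one

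*Protocol*

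**What the plan says.** Section 14.4.2 models six-month change in each progression endpoint, using a mixed model for continuous endpoints; "For dichotomous progression endpoints, a logistic regression model will be fit". In both cases "an initial model will consist of all baseline characteristics, an indicator variable for whether the subject is a PD patient or healthy control". The same starting model also takes in the interactions: "and all possible two-way interactions". Then: "We will utilize backwards selection to build a model for each progression endpoint". The section gives no cap on the list, no penalty and no validation.

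Section 14.4.3 asks whether short-term change predicts long-term MDS-UPDRS change. It admits only endpoints that differ between subsets, and "All progression endpoints that meet these criteria will be modeled using a process similar to that described above". Ten-fold cross-validation is stated there. Section 14.4.4 repeats the first three analyses within PD subsets.

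Section 14.5 gives 600 subjects (400 PD, 200 controls) for the PD versus control comparison, with table rows of 450 and 600 "when, respectively 75% and 100% of the subjects are available for analysis". For PD alone it gives 400, or 300 after withdrawals.

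**The concern.** The number of interactions grows with the square of the number of characteristics. A model holding all of them reaches the number of subjects quickly, and full-model backward elimination must first fit that model. Where it can be fitted with few subjects per coefficient, elimination at a nominal level keeps many chance terms, and the p-values of the survivors take no account of the search.

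This matters because 14.4.2 is the protocol's only described model for comparing short-term change between groups, and 14.4.3 passes forward only endpoints that show a difference. Section 14.4.3 also says that success would mark endpoints as valid biomarkers for later intervention studies, so chance findings here could shape future trials.

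**Working it through.** **Sample sizes.** The protocol states no coefficient count. Its nearest figures are the detectable standardized differences in 14.5, which confirm the N in use. With d = (1.960 + 0.842) × √(1/n₁ + 1/n₂):
- 150 v 150: 0.323 (stated 0.33)
- 200 v 200: 0.280 (stated 0.28)
- 300 v 150: 0.280 (stated 0.28)
- 400 v 200: 0.243 (stated 0.24)

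These agree to rounding, but they cover simple two-group comparisons, not the model building.

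**Size of the starting model.** Let b be the number of baseline characteristics, one coefficient each, and p = b + 1 with the group indicator. Coefficients = 1 + p + p(p−1)/2 = p(p+1)/2 + 1.

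| b | p | Coefficients | Compared with |
|---|---|---|---|
| 19 | 20 | 211 | 2.8 subjects each at N = 600; 2.1 at N = 450 |
| 23 | 24 | 301 | first to exceed 300 |
| 27 | 28 | 407 | first to exceed 400 |
| 29 | 30 | 466 | first to exceed 450 |
| 34 | 35 | 631 | first to exceed 600 |
| 50 | 51 | 1,327 | more than twice 600 |

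**How large b could be.** This is an assumption built from the protocol's own lists for measures taken in both PD and control subjects at screening or baseline:
- age, gender, family history: 3
- scales and tests in the Schedules of Activities: 16
- vital signs, height and weight (6.2.2): 7
- laboratory analytes (6.2.3): 22

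That is 48, or about 50 with DAT imaging, MRI and CSF or blood markers, before any subscores, imaging regions or genotypes. Without the laboratory values it is about 50 − 22 = 28, so p = 29 and 436 coefficients. That just fits in 450 subjects but exceeds the 300 to 400 PD subjects of 14.4.4. A simulated design with b = 50 and N = 600 had 1,327 columns and rank 600, so no unique fit exists.

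Repeated visits do not help. Baseline covariates and their interactions vary only between subjects, and interactions with time add further terms. Logistic models are tighter still, because events are fewer than subjects.

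**Narrow list.** Backward elimination was simulated from the 211-coefficient model with pure-noise outcomes. Assumptions: independent normal covariates, 2:1 group split, one continuous outcome per subject, 0.05 stay level, no hierarchy rule. Ranges are across repeated runs.
- N = 600: 14 to 15 terms kept on average, apparent R² 0.11 to 0.12
- N = 450: 14 to 18 terms kept on average, apparent R² 0.16 to 0.18
- At least one term involving group survived in 76 to 80% of noise endpoints; the group main effect itself survived in 7 to 12%

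With b = 28 and N = 600, a small run kept about 41 noise terms (apparent R² 0.28). With b = 10 it kept about 4 (0.04).

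**The case against.** **The count is assumed.** This stands. A reader might infer that the model certainly has more coefficients than subjects and that selection can never start. The protocol does not support that, because it lists no characteristics for 14.4.2. The laboratory tests sit under safety assessments, and the unseen Data Analysis Plan, to which 14.4 defers further detail, could name a short list. With 33 or fewer characteristics at N = 600, or 28 or fewer at N = 450, the model can be fitted. What does not fall away is overfitting, which is clear at 19 items. Nor is this only missing detail: the protocol already fixes all characteristics and all possible interactions, so a workable plan would have to override it.

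**Group and the filter.** A reader might infer that selection will discard the group term, or that the 14.4.3 filter is read off the selected model. The protocol says neither. It is silent on forced terms and on how a difference is judged, and 14.5 also mentions univariate assessments across groups. Reading 14.4.2 as the source of the filter is natural, but it is an inference.

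**Cross-validation exists.** It does, in 14.4.3 and by repetition in 14.4.4, so it would be wrong to say the predictive models are unvalidated. It is not stated for 14.4.2.

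**The work is exploratory.** Section 14.5 says so and offers no formal sample-size justification for the model building. The primary objective in 14.2, estimating rates of change, does not depend on this selection. That limits the consequence but does not make the procedure workable.

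**Section 14.4.7.** A reader might extend the point to events per variable in the phenoconversion model: "The examination will involve fitting a logistic regression model for phenoconversion, with each progression endpoint serving as a covariate". This can equally mean one covariate at a time, and the number of endpoints is nowhere stated, so no such figure can be supported.

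**Conclusion.** The point holds conditionally. On a long baseline list (34 or more characteristics at N = 600, 29 at N = 450, 23 at N = 300) the prescribed starting model cannot be fitted, and the protocol's own lists of about 45 to 50 items with laboratory values pass those limits. On a short list of about 19 it can be fitted, with 2 to 3 subjects per coefficient, but it keeps about 15 noise terms. In both cases the group effects and p-values from 14.4.2 cannot be relied on, and that section has no validation. The coefficient formula and sample sizes are firm. The number of characteristics is an assumption, and the simulation uses simplified data. The analysis wording should be changed; the primary estimation objective is not threatened.

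**What to change.** **Group comparison (14.4.2).** Use one fixed, pre-specified model per endpoint: baseline value, age, sex, group, and group × time where there are repeated measures. Always retain group and do no selection.

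**Visits.** Limit the six-month PD versus control comparison to endpoints that controls have at that visit, such as blood, urine and CSF markers. Section 5.3.6 excludes controls from the clinical scales at month 6, and the control Schedule of Activities next repeats MDS-UPDRS at month 12, so month 12 should be used for such endpoints. Controls have a DAT scan at screening only, so no model can compare DAT change with controls.

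**Filter.** State that this fixed-model test decides which endpoints enter 14.4.3.

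**Prediction (14.4.3, 14.4.4).** Start from main effects plus group-by-characteristic terms only. That is 1 + b + 1 + b = 2b + 2 coefficients: 40 for b = 19 and 102 for b = 50, both below 300. Use a shrinkage method (elastic net is one option) or a limited candidate list, and carry out all selection inside the stated ten-fold cross-validation.

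**Cost.** Wording and modest programming; no new subjects, visits or data. The downside is that fewer interactions are searched.

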| Statistical Methods | Changes from baseline to the one year, two year, three year, four year and five years evaluations will be calculated and summarized descriptively. We will calculate 95% confidence intervals for the mean rate of change and between subject variability, For this purpose the between subject variability will be estimated by fitting mixed models to all available data. Correlations will be calculated between the different measures, for example between change in total MDS-UPDRS and change in DAT uptake or alpha-synuclein levels.                                                                                                                                                                                                                                                                                                                                                                                                                                                                                                                                                                                                                                                                                                                                                                                                                                                                                                                                                                                                                                                                                                                                 |

|                    |                                                                                                                                                                                                                                                                                                                                                                                               |
|--------------------|-----------------------------------------------------------------------------------------------------------------------------------------------------------------------------------------------------------------------------------------------------------------------------------------------------------------------------------------------------------------------------------------------|

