### **3. Study Outcomes**

#### **3.1 Primary Outcomes**

The mean rates of change and the variability around the mean of clinical, imaging and biomic outcomes in early PD patients, and where appropriate the comparison of these rates between PD patient subsets and between various subsets (including, but not limited to: PD vs. healthy subjects, PD vs. SWEDD, PD vs. prodromal, PD with and without LRRK2, GBA or SNCA mutation, unaffected LRRK2, GBA or SNCA mutation carriers vs. healthy subjects) at study intervals ranging from 3 months to 36 months. Specific examples of outcomes include MDS-UPDRS, dopamine transporter striatal uptake, vesicular monoamine transporter type-2 uptake, and serum and CSF alpha-synuclein. PD patient subsets may be defined by baseline assessments, genetic mutation, progression milestones and/or rate of clinical, imaging, or biomic change.

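### Section 14.4.3 can overstate predictive validity: backward selection need not be repeated inside the cross-validation folds, and early and long-term MDS-UPDRS change may share a visit

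*Protocol*

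**What the plan says.** Section 14.4.2: "The second set of analyses will examine the short-term change during the first six months", for every progression endpoint. The starting model holds all baseline characteristics, a PD-or-control indicator and every two-way interaction, and is reduced by backward selection.

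Section 14.4.3 then asks "whether short-term changes in the progression endpoints are predictive of changes in long-term endpoints in the MDS-UPDRS score". Endpoints are kept only if they differ between subsets, and the survivors are modelled in a way described as similar to 14.4.2. On the outcome: "The primary focus will be on the long-term change in the UPDRS score". On the safeguard: "a ten-fold cross validation procedure will be used to test the predictive validity of each model". On success: "This would suggest that these short-term progression endpoints are valid biomarkers for future studies of interventions in PD patient populations". Section 14.4.4 repeats the whole sequence for subsets of PD subjects.

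Three further places matter:

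- Section 3.1 names MDS-UPDRS as an outcome ("Specific examples of outcomes include MDS-UPDRS, dopamine transporter striatal uptake"), and nothing in 14.4 bars it as a short-term predictor.
- Section 14.4.3 does not say at which visit long-term change starts. The Synopsis (Statistical Methods) says "Changes from baseline to the one year, two year, three year, four year and five years evaluations will be calculated and summarized descriptively".
- Section 14.4 opens by leaving further detail to a separate Data Analysis Plan, which is not at hand.

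**The concern.** Cross-validation measures predictive validity only if the held-out subjects played no part in building the model. The text runs screen, build, then test each model. Followed in that order, backward selection has already seen every subject's outcome, and refitting the surviving terms in nine tenths of the data does not undo that.

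Separately, if early MDS-UPDRS change is used to predict long-term MDS-UPDRS change and both are measured from Baseline, the Baseline error is subtracted from both. A subject scored too high by chance at Baseline appears to improve early and late. Held-out subjects carry the same coupling, so cross-validation cannot expose it.

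Finding progression markers for trials of disease-modifying therapy is the study's primary objective, and 14.4.3 is the step at which short-term endpoints would be described as valid.

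**Working it through.** **Part A: selection and folds.** The order of steps comes from 14.4.2 and 14.4.3. The sample comes from 14.5: 400 PD subjects less 25% withdrawals, 400 × 0.75 = 300. The number of candidate terms is not given. With k main effects and all pairwise interactions it is k + k(k−1)/2, so k = 4 gives 10, k = 10 gives 55 and k = 15 gives 120.

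Simulation: predictors and outcome are independent standard normal noise. Backward elimination runs to p < 0.05 (assumed threshold). Ten-fold R² = 1 − SSE/SST, with selection either once on all data or afresh in each training set.

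| n | Terms | Runs | Mean R², selection on all data | R² > 0 | Mean R², selection in folds | R² > 0 |
|---|---|---|---|---|---|---|
| 300 | 10 | 150 | −0.001 | 35% | −0.019 | 7% |
| 300 | 20 | 100 | 0.005 | 58% | −0.031 | 7% |
| 300 | 55 | 50 | 0.026 | 88% | −0.077 | 0% |
| 300 | 120 | 15 | 0.063 | 100% | −0.211 | 0% |
| 400 | 55 | 50 | 0.020 | 86% | −0.057 | 2% |

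A separate simulation at n = 300 with 30, 60 and 150 terms (200, 120 and 40 runs) gave mean R² of 0.02, 0.04 and 0.10, positive in 80%, 92% and 100% of runs. With selection inside the folds it was positive in 0–7%.

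The subset screen was tested alone: 50 noise markers, 300 PD against 150 controls, t-test at 0.05, then a PD-only model with no further selection. Mean ten-fold R² was −0.016. The optimism therefore comes from outcome-based backward selection, not from the screen.

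**Part B: shared visit.** The protocol gives no figure for this validation. The nearest is the detectable correlation in 14.5. Taking the 0.80 there as power, tanh((1.960 + 0.842)/√(N−3)) gives 0.161, 0.140, 0.132 and 0.114 for N = 300, 400, 450 and 600, against the stated 0.16, 0.14, 0.14 and 0.11. The 450 row differs by 0.01, which has no bearing here.

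Write early change as s + e6 − e0 and long-term change as L + eL − e0, where s and L are true changes and the e terms are independent visit errors. With no link between s and L, the covariance is var(e), so

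r = var(e) / √[(2var(e) + var(s)) × (2var(e) + var(L))].

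The protocol gives no variances. Assume error SD 3–6 points, true six-month SD 0–4 and later true SD 6–12, with var(L) the sum of the six-month and later variances. Only the shared-error part is counted in the numerator.

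- Low end (3, 4, 12): 9/√(34 × 178) = 9/77.8 = 0.12.
- High end (6, 0, 6): 36/√(72 × 108) = 36/88.2 = 0.41.

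On a second grid of assumed variance ratios, at n = 300:

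| var(s)/var(e), var(L)/var(e) | r | Power to declare it significant | Mean ten-fold R² |
|---|---|---|---|
| 0.5, 1 | 0.37 | about 100% | 0.120 |
| 1, 2 | 0.29 | 99.9% | 0.072 |
| 1, 4 | 0.24 | 98.5% | 0.045 |
| 1, 8 | 0.18 | 89% | 0.024 |
| 2, 16 | 0.12 | 53% | 0.003 |

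Adjusting for the observed Baseline score reduces r without removing it: 0.28–0.34 in the first row and 0.08–0.11 in the last, for true between-subject variance of 2 to 9 times var(e).

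If the outcome starts at Month 6 instead, e6 enters the two changes with opposite signs and the covariance becomes −var(e). It is zero only when the two changes share no visit.

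**Route of entry.** Section 5.3.6 and the healthy-control schedule show no Month 6 MDS-UPDRS in controls, so its six-month change cannot pass a PD-versus-control screen. It can enter through comparisons with SWEDD or prodromal subjects, or through the PD subsets of 14.4.4.

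**The case against.** The strongest reply is that neither defect is written down. A reader might infer that the protocol selects once on the full data, or that it fixes Baseline as the start of long-term change. It does neither. Repeating selection in each fold fits the wording of 14.4.3, and the Synopsis sentence on change from baseline concerns descriptive summaries. Both details could sit in the Data Analysis Plan. This stands, and it is why the point is that 14.4.3 can overstate, not that it does. It does not dispose of the point, because the protocol itself sets the order of steps, the safeguard and the inference.

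A reader might also infer that the shared visit undermines the whole validation. It does not: imaging and biomic predictors are untouched, and the control schedule closes one route even for MDS-UPDRS.

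The sizes are open to challenge, and that also stands. Term counts and variances are assumed, and the simulated terms are independent noise rather than true interactions. The correlation formula uses two-point changes, whereas 14.4.2 plans a mixed model, and PD subjects also have a Month 3 score. A positive R² is not a stated success criterion, and 0.02–0.04 would be weak evidence for a marker. However, 14.4.3 states no other bar.

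Finally, 14.5 calls the analyses exploratory and looks to follow-up studies, and 14.4.3 says only that success would suggest validity. The documents do not support reading this as a plan for trials to adopt markers directly from this step.

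**Conclusion.** The point holds in a limited form. As ordered, 14.4.3 allows outcome-based selection on all subjects before validation. If done that way, noise gives a positive ten-fold R² in 58–100% of runs at n = 300 with 20 or more candidate terms, against 0–7% with selection inside the folds. The mean is about 0.03 at 55 terms and near zero at 10, so the size depends on how many baseline characteristics enter, which the protocol does not say.

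The shared-visit point is secondary and conditional. It needs early MDS-UPDRS change as a predictor, entry through a comparison without controls, and both changes taken from Baseline. The induced correlation is then about 0.12 to 0.41 under assumed variances, around or above the 0.16 that 14.5 gives as detectable at 300. With large true variance it becomes small.

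**What to change.** State in 14.4.3 that all outcome-based backward selection is repeated inside each of the ten training folds, and that only this nested estimate is used to judge predictive validity. The cost is computing time and a less favourable estimate. No data collection changes. The subset screen need not be the target, since alone it produced no optimism in a PD-only model.

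Where early MDS-UPDRS change predicts long-term MDS-UPDRS change, add an analysis in which the two changes share no visit. There are two options:

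- **Use the Screening score, already collected in PD subjects, as the origin of one change.** This keeps the full outcome interval. It relies on Screening and Baseline errors being independent, and the true change of the first six months still lies within both intervals.
- **Start the outcome at a visit after Month 6.** This removes the overlap but shortens the outcome interval. PD medication may have begun by then: section 7.1.1 anticipates only that most subjects stay off it for at least six months, and section 5.3.24 lets a symptomatic-therapy visit replace a scheduled one.

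Because each option has a price, this belongs as an added analysis for that one predictor, not as a new definition of the outcome for all markers.

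### In Protocol 14.4.3, cross-validation of a pooled PD and healthy-control model can succeed on PD status alone, so it does not show that a retained marker predicts progression among PD patients

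*Protocol*

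**What the plan says.** Protocol 14.4.2 describes the model for each short-term (six-month) endpoint. It starts from all baseline characteristics, "an indicator variable for whether the subject is a PD patient or healthy control, and all possible two-way interactions", and is then reduced: "We will utilize backwards selection to build a model for each progression endpoint".

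Protocol 14.4.3 turns to long-term change, chiefly in the MDS-UPDRS. It first screens the markers: "Only progression endpoints that show differences between subsets will be considered". It then refers back to the earlier procedure: "All progression endpoints that meet these criteria will be modeled using a process similar to that described above". As a safeguard, "a ten-fold cross validation procedure will be used to test the predictive validity of each model". The outcome, with respect to the long-term endpoints, is described as follows: "If successful, the final model will provide a subset of one or more short-term progression endpoints that are predictive of the change". The inference drawn is: "This would suggest that these short-term progression endpoints are valid biomarkers for future studies of interventions in PD patient populations".

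Protocol 14.4.4 adds: "Each of the first three sets of analyses will be repeated comparing subsets of PD subjects, rather than PD subjects vs. healthy subjects". This indicates that 14.4.3 itself is a PD-versus-healthy analysis.

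**The concern.** What is validated is not what is concluded. Cross-validation is applied to the predictive performance of the whole model in a sample that mixes patients and controls. The conclusion is about whether particular markers predict progression among patients.

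PD status can be expected to predict change on a PD rating scale. A model that contains it, or a marker that stands in for it, can therefore predict out of sample even if no marker carries information within PD. The screen for group differences does not help, because it favours markers that track diagnosis.

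The stake is which short-term markers are carried forward as candidates for trials of disease-modifying therapies, the use named in the overall objective (Protocol 2.1).

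**Working it through.** The protocol gives no figure for this analysis, so there is none to reproduce.

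**Inputs from the protocol.** 400 PD and 200 controls, or 300 and 150 when 75% are available (14.5). Model terms and backwards selection come from 14.4.2, and ten-fold cross-validation from 14.4.3.

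**Assumptions, not in the protocol.** PD–control difference in long-term MDS-UPDRS change, d = 0.3 to 1.2 within-group SDs. Marker difference between groups, m = 0.28 to 0.8 SD, with zero marker–outcome association within each group. Terms retained at p < 0.05. Success means cross-validated R² above zero.

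**1. What PD status alone explains.** With a PD share p = 2/3, p(1−p) = 0.222 and R² = 0.222d² / (1 + 0.222d²).

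| d | calculation | R² |
|---|---|---|
| 0.3 | 0.020/1.020 | 2.0% |
| 0.5 | 0.0556/1.0556 | 5.3% |
| 0.8 | 0.142/1.142 | 12.5% |
| 1.2 | 0.320/1.320 | 24.2% |

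**2. Pooled correlation of a marker that is null within groups.** r = 0.222dm / √[(1 + 0.222d²)(1 + 0.222m²)].
- d = 0.3, m = 0.28: 0.0187/√(1.020 × 1.017) = 0.02.
- d = 1.2, m = 0.8: 0.213/√(1.320 × 1.142) = 0.17.

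Group membership alone produces these correlations.

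**3. Whole-model cross-validation with a null marker** (300 PD + 150 controls, indicator in the model, 400 runs per setting).
- Pooled R² > 0 in 84–86% of runs at d = 0.3, and in 99.8–100% at d = 0.5 or more.
- PD only (n = 300): mean cross-validated R² about −0.003, above zero in 17–22% of runs.

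**4. Gain from the marker.** Mean pooled cross-validated R² with the marker against the indicator alone: 0.046 v 0.049 (d = 0.5), 0.119 v 0.121 (d = 0.8), 0.240 v 0.241 (d = 1.2). The marker adds nothing, and only a comparison of this kind reveals it.

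**5. How often a null marker survives selection.**
- Main effects only: 4–7% of runs, about the nominal 5%.
- All two-way interactions (200 runs per setting, d = 0.5 to 1.2): some marker term is kept in 20–24% of runs with 3 baseline characteristics, 25–29% with 5 and 47–51% with 10.
- Cross-validation run after selection rejected none of these models.
- With selection repeated inside each fold, a marker term was kept and the model passed in 20–24%, 25–29% and 22–51% of runs respectively.
- The 22% arises with 10 characteristics at d = 0.5, where only 45% of all models passed. Since 0.45 × 0.47 = 0.21, the rejections reflect general overfitting and do not single out the useless marker.

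**6. Many markers.** If M independent null markers are each tested at 5%, at least one is kept with probability 1 − 0.95^M: 23% for 5, 40% for 10, 64% for 20.

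**7. Which endpoints are affected.** A pooled fit needs six-month change in both groups. In Protocol 5.3.6 the month-6 rating scales and questionnaires are not done in controls, and the control schedule has DAT and VMAT-2 imaging only at screening. Controls do give blood, urine and CSF at baseline and month 6, and have annual MDS-UPDRS ratings for the long-term outcome.

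**The case against.** A reader might infer that useless markers are automatically declared valid. The documents do not support that. With the indicator in the model, a null marker's main effect is tested within groups and dropped about 95% of the time. A model that passes says nothing in favour of a marker that selection has removed. False declarations arise from chance retention across many markers or interactions, and much of their frequency is ordinary multiplicity (step 6). What remains is that the pooled validation does not remove them.

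Other points against the concern have weight:

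- The indicator in 14.4.3 is inferred from the reference back to 14.4.2 and from 14.4.4; it is not written there. Omitting it would not help: the null marker alone then gives cross-validated R² > 0 in 21–99.8% of runs.
- The protocol sets no success threshold and defers details to the PPMI Data Analysis Plan. That absence is no fault. However, a threshold on whole-model accuracy in a mixed sample can be met wholly or partly through PD status, so setting one does not cure the mismatch.
- 14.4.4 repeats the work among PD subjects without controls. This is a real mitigation, but it compares PD subsets and the 14.4.3 conclusion does not depend on it.
- The inference is worded as a suggestion, 14.5 describes much of the plan as exploratory, and the primary objective in 14.2 concerns rates of change. These points lower the priority.

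**Conclusion.** The concern holds in a limited form. As 14.4.3 is most naturally read, passing cross-validation is not evidence that a retained short-term marker predicts long-term MDS-UPDRS change among PD patients, yet that is the conclusion drawn. Under the stated assumptions a pooled model with an uninformative marker passes in 84–100% of runs, against 17–22% when validated in PD alone.

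These rates depend on the assumed group differences, on taking R² > 0 as success, and on the inferred indicator. The survival rates in step 5 also depend on the assumed 0.05 retention level and the number of baseline characteristics.

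The scope is endpoints with six-month change in both groups, mainly blood, urine and CSF markers. Because the analysis is exploratory, this is a worthwhile correction and does not undermine the study's primary estimates.

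**What to change.** In Protocol 14.4.3:

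- Fit and cross-validate the long-term models in PD subjects only, keeping the PD-versus-control comparison as the earlier screen.
- Judge success by the gain in cross-validated prediction over the same model without the short-term marker.
- Limit the concluding sentence to markers that predict progression in PD.

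The base covariates and the size of gain required can stay with the Data Analysis Plan. A bar of merely above zero would be lenient, since a single null marker in PD cleared it in 17–22% of runs.

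The cost is a wording change and one nested-model comparison, with no new data. The downside is lower apparent predictive accuracy, because the part due to diagnosis is removed.
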